## Hypotheses

The following hypotheses will be tested:

1. The criteria on structure and process should be achieved by all participating clinics and NGO;
2. More patients with DM will achieve the target HbA1c after 12, 24, 36 and 48 months in the PEP programme;
3. More patients with HT or DM will achieve the target blood pressure levels after 12, 24, 36 and 48 months in the PEP programme;
4. In longer terms, HT/ DM patients will have reduced cardiovascular risks and fewer complications;
5. Patients should report an improvement in quality of life (QOL), enablement and overall health condition after the PEP programme;
6. Patients who take part in PEP programme should not have any increase in service utilization rates.

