## Subjects

All patients who have been enrolled into the PEP programme will be included in the evaluation on process of care for each audit cycle; whereas all enrolled subjects who have been recruited for more than 12 months in the programme will be included in the evaluation on the clinical outcomes of care for each audit cycle.

To determine a difference of programme performance and impact between group (PEP participants and non-participants). A cohort of all eligible DM patients under care of HA GOPC at 1 Sep 2009 would be included for the monitoring of the changes in clinical and service utilization outcomes from Sep 2009 to Sept 2015.

550 patients who have enrolled into the PEP and 550 who have not taken part in the PEP will be invited in person from the general outpatient clinics by trained research assistants at the beginning of each evaluation cycle to take part in a telephone survey on patient reported outcomes for each cluster and written consent will be obtained (appendix A). All subjects who have given consent to the telephone follow-up survey will be interviewed by telephone within four weeks, at 6, 12, 36 and 60 months from recruitment to answer the SF-12 Health Survey on quality of life (QOL), the patient enablement Instrument, the Global Rating Scale (GRS) change in health, and a structured questionnaire on private service utilization rates.

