## Data Collection

Evaluation on structure and process

The co-ordinator of each participating clinic and all participating NGO will be asked to complete the structure of care questionnaire (appendix B). Anonymized data will be retrieved from the computerized medical record system (CMS) by the HA Statistics team to determine the patient recruitment rate, enrollment rate, attendance rate, compliance with assessment as per protocol, number of investigations and referral rate.

Evaluation on outcomes of care

Anonymized data on HbA1c, blood pressure (BP), low-density lipoprotein (LDL), body mass index (BMI) and annual attendance rates for GOPC, specialist outpatient clinic (SOPC) , accident and emergency (A&E) and hospital attendance rates, patient knowledge on disease at baseline and 12 months will be retrieved from the CMS by the HA Statistics team. The audit cycle will be repeated annually over a period of 5 years. This data will be extracted are shown in the data collection form in appendix C.

The 550 patients in the PEP programme who are willing to take part in the telephone survey will be contacted by a trained research assistant who will obtain verbal consent from each patient. Each patient will then answer the Chinese (Hong Kong) Short Form-12 version 2 (SF-12v2) Health Survey within one month from enrolment, and then at 6, 12, 36 and 60 months to repeat the SF-12v2 together with the Patient Enablement Instrument (PEI), Global Rating Scale (GRS) of change in health condition and private service utilization (appendix D).

- 1. The Chinese (Hong Kong) Short Form-12 version 2 (SF-12v2) Health Survey is a generic measure HR QOL. It has been validated and normed on the general Chinese population in Hong Kong (Lam, Wong et al. 2010). It measures eight domains on physical functioning, role physical, bodily pain, general health, vitality, social functioning, role emotional and mental health on a scale range from 0 to 100. A higher score indicates better HRQOL. The eight domain scores can be summarized into two summary scores, the physical (PCS) and mental (MCS) component summary.

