## Outcome measures

**Primary**

- The proportion of clinics/NGO that have satisfied each of the set structure criteria.
- The proportion of patients who have complied with the criterion process of care.
- The proportion of DM patients who have achieved a HbA1c level <7%.
- The proportion of HT/ DM patients who have achieved the target blood pressure.
- The estimated 10-year cardiovascular disease risk.

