**Secondary**

- Clinical outcomes including LDL and BMI.
- Cardiovascular complications.
- Renal complications.
- Patient reported outcomes (PRO) measured by the change in SF-12v2 scores, the PEI and GRS scores at 6, 12, 36 and 60 months, and change in patient’s knowledge on disease at 12 months.
- GOPC consultation, SOPC, A&E and hospital attendance rates in the past 12 months; the audit cycle will be repeated annually over a period of 5 years.

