## Appendix C: Data collection form for extraction of data from the HA medical records

| **Data Required** | **Number of  patients** | **Time (in days) from recruitment** |
| --- | --- | --- |
|
| Uptake of programme* | | |
| Patients identified eligible |  | NA |
| Patients recruited |  | NA |
| Patients enrolled |  |  |
| Process of care* | | |
| Patients attended at least 1 generic session |  |  |
| Patients attended at least 1 disease specific session |  |  |
| Patients completed the programme |  |  |
| Patients dropped out or discharged from programme |  |  |
| Patients identified to have problems (e.g. poor drug compliance, overweight, foot deformity, smoking) |  |  |

*include only subjects who have enrolled more than 12 months

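### The specified record extract has no fields for the cardiovascular and renal complications and lacks usual inputs for the primary 10-year risk; its 12-month footnote spoils the uptake rates and conflicts with the stated process population.

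*Protocol*

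**What the plan says.** Under Outcome measures, the protocol lists "The estimated 10-year cardiovascular disease risk" among five primary outcomes. The secondary list includes "Cardiovascular complications" and "Renal complications". Hypothesis 4 depends on all three: "In longer terms, HT/ DM patients will have reduced cardiovascular risks and fewer complications".

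The source for these is the record extract described in Data Collection. The narrative list there begins "Anonymized data on HbA1c, blood pressure (BP), low-density lipoprotein (LDL), body mass index (BMI) and annual attendance rates for GOPC" and goes on to other attendance rates and disease knowledge. It then hands over to the form: "This data will be extracted are shown in the data collection form in appendix C".

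In Appendix C, the uptake block and the process-of-care block both carry an asterisk, and the footnote reads "include only subjects who have enrolled more than 12 months". The Subjects section gives a different rule: "All patients who have been enrolled into the PEP programme will be included in the evaluation on process of care for each audit cycle". It reserves the 12-month condition for clinical outcomes. The Abstract applies a more-than-one-year condition to process and outcomes alike.

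**The concern.** There are two separate defects in the same form.

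The first is that named outcomes have no matching field. A statistical analysis plan can choose the risk equation and define a complication, but it cannot analyse items that were never requested. The data arrive anonymized from the Hospital Authority's statistics team, so linking further items afterwards may be awkward. At stake are one primary outcome, two secondary outcomes and hypothesis 4.

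The second is that the footnote restricts blocks where the restriction does harm. Uptake needs the people who did not enrol in its denominators, and the footnote removes them. For process of care, also a primary outcome, the protocol gives two different populations, so two analysts could report different proportions and each be following the text.

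**Working it through.** **Fields against outcomes.** No arithmetic applies here. The check sets each outcome beside the fields specified for it.

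| Outcome | Specified fields that help | Not specified |
| --- | --- | --- |
| 10-year cardiovascular risk (primary) | systolic and diastolic BP, BMI, HbA1c, LDL-C | age, sex, patient-level smoking status; further inputs depend on the equation |
| Cardiovascular complications (secondary) | none; the hospitalization count carries no cause | any diagnosis or event, with date |
| Renal complications (secondary) | none | any diagnosis, event or renal measure |

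Two places might have filled the gap:

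- Appendix C mentions smoking, but only as one example inside a single count of patients found to have problems. That gives no smoking status for an individual.
- Appendix D asks about smoking, but only of consenting telephone-survey participants. Its demographic questions cover marital status and income, not age or sex.

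The Abstract does say that the diabetes cohort will be followed for lipids and complication rates. The intention is therefore stated, but it reached neither the Data Collection list nor the form.

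**Footnote and uptake rates.** Data Collection asks for a recruitment rate and an enrolment rate, and Data analysis item 1 for the percentage enrolled. The uptake rows of Appendix C are eligible, recruited and enrolled. Let S be the number of subjects enrolled more than 12 months. Assuming that every enrolled subject was first eligible and recruited, restricting all three rows to these subjects gives eligible = recruited = enrolled = S. Then:

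- recruited / eligible = S / S = 100%
- enrolled / recruited = S / S = 100%

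The protocol gives no flow figures, so the illustration below uses assumed ones:

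| Eligible / recruited / enrolled / enrolled >12 months | True recruited/eligible | True enrolled/recruited | Both rates under the footnote |
| --- | --- | --- | --- |
| 1000 / 600 / 400 / 300 | 600/1000 = 60% | 400/600 = 67% | 300/300 = 100% |
| 1000 / 300 / 150 / 100 | 300/1000 = 30% | 150/300 = 50% | 100/100 = 100% |
| 1000 / 900 / 800 / 700 | 900/1000 = 90% | 800/900 = 89% | 700/700 = 100% |

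Three very different programmes look the same. The result concerns these rows only; attendance, completion and dropout can still vary.

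**Process population.** Subjects: all enrolled patients. Appendix C footnote: only those enrolled more than 12 months. Abstract: more than one year. Two places agree against one, and nothing in the protocol says which governs.

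**The case against.** The strongest reply is that Appendix C is not a complete data specification. It has no row for the number of investigations that Data Collection expects, gives patient-reported scores at 0 and 6 months only while the text runs to 60, and defines an abbreviation (KAP) that it does not use. A fuller specification may exist elsewhere. Eligibility already excludes severe heart failure and end-stage renal failure, so diagnostic information is evidently available. This stands as far as it goes: the documents do not show that the data are unobtainable. It does not remove the mismatch, because the narrative list in Data Collection has the same gaps and the text says that the form shows what will be extracted.

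A reader might infer that no patient could have a computable risk, or that these outcomes will be missing for everyone. The documents do not support that. No equation is named, several likely inputs are on the form, and the Abstract plans to follow complications. The need for age, sex and smoking status is an assumption about usual scores.

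A reader might also infer that adjustment for confounding would fail for want of age and sex. The between-group comparisons in Data analysis are t-tests and chi-square tests, so that is not a consequence for the plan as written.

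On the footnote, a looser reading (a calendar cohort with at least 12 months elapsed) would give meaningful uptake rates. That may be what was meant, but the words restrict subjects by their own enrolment. A 12-month rule is also defensible for completion and dropout, and the Abstract supports it, so the documents do not settle in favour of the Subjects section. Nor do they support a claim that a fixed share of process records is lost: the enrolment pattern is not given, and with annual cycles those patients enter at the next one.

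**Conclusion.** The point holds as an inconsistency within the protocol. Followed as written, the extract gives no source field for either complication outcome, whatever risk equation is chosen. It also lacks inputs that usual scores need for one of the five primary outcomes. Hypothesis 4 rests on all three. The first statement needs no outside assumption; the second assumes that the chosen score uses age, sex and smoking status.

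The footnote, read literally, fixes the recruitment and enrolment rates at 100% whatever the true flow. It also leaves a second primary outcome, the process-of-care proportion, with two conflicting populations. The 100% result rests on the literal reading; the conflict of populations is explicit.

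Nothing here shows that the records lack the data or that the harm is irreversible. The correction is cheap and is best made before the extract is requested.

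**What to change.** 1. Add to the Appendix C extract, for programme participants and cohort controls alike, dated cardiovascular and renal diagnoses or events, and the inputs of the chosen 10-year risk equation: at least age, sex and patient-level smoking status, with any further inputs the equation needs. Name the equation, and bring the Data Collection list into line with the form.
2. Remove the footnote from the uptake block, so that eligible, recruited and enrolled are counted on everyone identified.
3. Reconcile the Subjects section, the Abstract and the footnote to one stated population for the primary process-of-care proportion. If all enrolled patients are used, report completion and dropout for those with 12 months of follow-up.

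The cost is a wider query on existing records, one revised form and matching edits to the text. No additional patient contact is needed.

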**Secondary**

- Clinical outcomes including LDL and BMI.
- Cardiovascular complications.
- Renal complications.
- Patient reported outcomes (PRO) measured by the change in SF-12v2 scores, the PEI and GRS scores at 6, 12, 36 and 60 months, and change in patient’s knowledge on disease at 12 months.
- GOPC consultation, SOPC, A&E and hospital attendance rates in the past 12 months; the audit cycle will be repeated annually over a period of 5 years.

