**Abstract**

**Objectives:** The aim of this study is to evaluate the quality of care (QOC) of the Hospital Authority’s (HA) patient empowerment programme (PEP) programme using an evidence-based structured and comprehensive evaluation framework to identify areas for quality enhancement.

**Design, Setting and Subjects:** A longitudinal study will be conducted using the Action Learning and Audit Spiral methodologies to measure whether the target standard of care intended by the PEP programme is achieved. Each PEP participating clinic and non-government organization (NGO) will be invited to complete a structured evaluation questionnaire. The data of all patients who have enrolled into the PEP for more than one year will be included in the evaluation on the process and outcomes of care. To determine a difference of programme performance and impact between group (PEP participants and non-participants), cohort study would be adopted. A cohort includes all eligible DM patients under care of HA GOPC at 1 Sep 2009 will be followed up on the clinical outcomes including HbA1c, blood pressure, lipids, and complications rates. To evaluate the effect of PEP on patient-reported outcomes, 550 participants, as well as 550 of those who have not participated in the PEP, will be recruited from each cluster and followed up by telephone to evaluate the effect of the programme on quality of life (QOL), patient enablement, global rating of change in health condition and private service utilization at baseline, 6, 12, 36 and 60 months after enrolment. Data on the process of care will be retrieved from the HA medical records. The cost effectiveness analysis (CEA) by mathematical modeling will be carried out by using cost and clinical outcome data provided by the HA, as well as quality-of-life and private service utilization cost data collected by the telephone surveys.

**Main Outcome Measures:** The primary outcomes are the proportion of participants who have received the planned process of care and achieved the target HbA1c and blood pressure levels.

**Data Analysis:** Descriptive statistics on proportions meeting the QOC criteria will be calculated. The changes in clinical, service, and patient reported outcomes at 6 and 12 months will assessed by paired sample t-test for each audit cycle. The audit cycle will be repeated annually over a period of 5 years.

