## Data analysis

1. Descriptive statistics on standard of care will be calculated, including percentage of centers meeting each structure criterion, percentage of subjects enrolled, dropped out, completion of the programme, receiving criterion process, investigations and referral per protocol, and percentage of subjects achieving the criterion outcome.
2. The change in clinical, service, and patient reported outcomes after the PEP programme at baseline, 6, 12, 36 and 60 months will be compared by paired sample t-test. The audit cycle will be repeated annually over a period of 5 years.
3. Independent sample t-test or Chi square test as appropriate will be used to compare the clinical and service utilization outcomes between PEP patients and controls.
4. Independent sample t-test or Chi square test as appropriate will be used to compare the clinical and service utilization outcomes between results in achieved in different audit cycles.
5. Cost effectiveness analysis (CEA) by mathematical modeling will be carried out by using cost and clinical outcome data provided by the HA, as well as quality-of-life and private service utilization cost data collected by the telephone surveys.

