**Patients require special treatment:**

| **Data Required** | **Number of  patients** | **Time (in days) from problem recognition** |
| --- | --- | --- |
|
| Identified to have problem being given treatments per protocol |  |  |
| Referred for additional service |  |  |
| Refused additional service |  |  |

| **Time (Month)** | **Data required** |
| --- | --- |
| 0, 12, 24, 36 and 48 | **Clinical data** |
| HbA1c |
| Systolic BP |
| Diastolic BP |
| BMI |
| LDL-C |
| **Service utilization** (in the past 12 months) |
| Number of hospitalization |
| Number of A&E attendance |
| Number of GOPC consultation |
| Number of SOPC consultation |
| 0 and 6 months | **Patient reported** |
| Disease knowledge score |
| QoL score |
| PEI* |
| GRS* |

BP = Blood Pressure; BMI = Body Mass Index; LDL-C = Low density Lipoprotein Cholesterol; GOPC = General Outpatient Clinic; SOPC = Specialist Outpatient Clinic; KAP = Knowledge, Attitude and Practice.

*Measured at 6 months only.

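### The record extraction lists no death, exit from HA care or complication, so the within-patient test of service use loses patients who die or leave, and the complication comparison ignores time at risk

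*Protocol*

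**What the plan says.** The Subjects section fixes the comparison cohort on one date: "A cohort of all eligible DM patients under care of HA GOPC at 1 Sep 2009 would be included", for "monitoring of the changes in clinical and service utilization outcomes from Sep 2009 to Sept 2015". The Abstract adds that this cohort is "followed up on the clinical outcomes including HbA1c, blood pressure, lipids, and complications rates".

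Two hypotheses depend on that follow-up. Hypothesis 4 reads "In longer terms, HT/ DM patients will have reduced cardiovascular risks and fewer complications". Hypothesis 6 reads "Patients who take part in PEP programme should not have any increase in service utilization rates".

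Under Outcome measures, Secondary, cardiovascular and renal complications are listed without definition, and service use is "GOPC consultation, SOPC, A&E and hospital attendance rates in the past 12 months". Death is neither a primary nor a secondary outcome.

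The Data Collection section names Appendix C as the form showing what is extracted. That form takes HbA1c, blood pressure, BMI, LDL-C and four service counts, such as "Number of hospitalization", at months 0, 12, 24, 36 and 48. Its one exit item concerns leaving the PEP programme. It has no item for death, last HA contact, leaving HA care or any complication.

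Data analysis item 2 compares outcomes over time by paired t-test. Item 3 says that an independent t-test or chi-square test "will be used to compare the clinical and service utilization outcomes between PEP patients and controls". Neither item mentions person-time or censoring.

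**The concern.** A closed cohort of people with diabetes, followed for six years, will lose members to death and to care elsewhere. A count that looks back over a year from an anniversary suits patients who are still there at the anniversary. A paired test needs a value at both ends. Together, as written, they remove from the within-patient comparison those who die or leave, along with their attendances since the last anniversary. If attendances rise as death approaches, the comparison leans towards the result that hypothesis 6 predicts.

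For hypothesis 4, a chi-square test compares proportions with an event as if everyone had been watched for the same time. Whether a fatal cardiovascular or renal event is a complication is left open.

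The choice of model could be left to a statistical analysis plan. The data items could not: an analysis plan cannot use a death date that was never requested. Because the HA Statistics team supplies the data in anonymised form, adding the date later may be difficult.

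**Working it through.** **The plan's own figure.** The only calculation in the protocol is for the telephone survey: 175 per group for an effect size of 0.3 at 80% power. The normal approximation at two-sided 5% gives 175, and four losses of 25% give 175 / 0.75^4 = 553, against the stated 550. It reproduces closely, but it does not concern the record cohort and gives no mortality.

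**Following one patient through the form.** Suppose a patient dies at month 20.
- Values exist for months 0 and 12.
- Attendances in months 12 to 20 belong to the month-24 look-back, which this patient does not reach.
- The pair (0, 24) is incomplete, so the paired t-test omits the patient. The same holds for a patient who leaves HA care at month 20.
- With counts alone, a patient who died, one who left and a living patient with no attendances may look the same at a later anniversary.

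**How many patients.** The documents give no mortality, so annual mortality m is assumed. Deaths by year t = 1 − (1 − m)^t. Both horizons are shown because the form stops at month 48 while the cohort runs six years.

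| m (assumed) | dead by month 48 | dead by year 6 |
| --- | --- | --- |
| 1% | 1 − 0.99^4 = 3.9% | 1 − 0.99^6 = 5.9% |
| 2% | 1 − 0.98^4 = 7.8% | 1 − 0.98^6 = 11.4% |
| 4% | 1 − 0.96^4 = 15.1% | 1 − 0.96^6 = 21.7% |

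Loss from HA care for other reasons would add to these figures. The documents give no rate for it.

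**Within-patient comparison.** Let a survivor's yearly use be 1, unchanged since baseline, and let a patient who dies use k times as much in the year of death (k assumed). Mean use per patient alive at the start of the year is (1 − m) + mk. Among survivors alone it is 1.00.
- m = 1%: k = 2 gives 1.01, k = 10 gives 1.09.
- m = 2%: k = 2 gives 1.02, k = 5 gives 1.08, k = 10 gives 1.18.
- m = 4%: k = 2 gives 1.04, k = 10 gives 1.36.

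The paired test on survivors would show no change in every case. These figures suppose that all use in the year of death is left out. They show the direction and are not estimates.

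**Between-group comparison.** Let survivors' use be equal in both groups, so that the survivor-only ratio is 1.00.
- PEP 2%, controls 3% a year: the all-patient ratio is 1.02/1.03 = 0.99 at k = 2 and 1.18/1.27 = 0.93 at k = 10. Omitting deaths hides an advantage of PEP.
- PEP 3%, controls 2%: 1.03/1.02 = 1.01 at k = 2 and 1.27/1.18 = 1.08 at k = 10. Omitting deaths hides a disadvantage.

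The direction therefore depends on which group has the higher mortality, which the documents do not say.

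**Complications.** The Abstract counts complication rates among the clinical outcomes, so item 3 of Data analysis applies, and for a yes/no outcome that means chi-square. A patient who dies in year 1 without a recorded complication counts as event-free, with the same weight as one followed to the end. If fatal events are not counted, the group with more fatal events looks better on complications. No complication item on the form shows how or when events would be captured.

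**The case against.** The best defence is that the form is not the whole extraction. It omits complications, which are listed outcomes, and it reads like the annual programme audit form, so the absence of a death date from it does not prove that none will be obtained for the 2009 cohort. HA records could also supply the attendances of patients who later died, and the word rates leaves room for a person-time denominator. This stands as far as it goes: the data may exist. But Data Collection presents Appendix C as what will be extracted, and nothing else in the protocol requests these items or sets a person-time denominator.

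A second defence is that negative binomial models, censoring and competing risks are normally left to an analysis plan. That is fair for the choice of model. It does not cover data items that the extraction omits.

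A reader might also infer more than the text supports:
- That fatal events are excluded from complications. The protocol does not define complications, so it neither includes nor excludes them.
- That service use before death is certain to be lost, and that both hypotheses are tested on survivors only. This follows for the paired service-use test. For complications and the independent-sample tests it is a risk.
- That mortality must differ because PEP excludes severe heart failure and end-stage renal failure. The cohort consists of eligible patients, so on a natural reading the same exclusions apply to both groups. Mortality may differ because participation is voluntary and not randomised, but the documents do not show that it does.
- That every comparison is tilted in favour of PEP. Only the within-patient comparison has a predictable lean, and only if use rises before death.

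**Conclusion.** The point holds in this form. The extraction form lists no death, no exit from HA care and no complication for a cohort followed for six years. As written, the paired test of hypothesis 6 loses patients who die or leave between anniversaries and leans towards no increase if use rises before death. The complication part of hypothesis 4 and the between-group comparisons are exposed to bias in either direction, through unequal time at risk and an undefined complication outcome.

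The size cannot be taken from the documents. Under assumed mortality of 1% to 4% a year, about 4% to 15% of the cohort would be dead by month 48 and 6% to 22% by year 6. The effect on any service-use contrast also depends on an assumed level of use before death. Service use and complications are secondary outcomes. The change should still be made before extraction, because later analysis cannot recover what was not requested.

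**What to change.** Add to the extraction, for participants and non-participants alike: date of death, cause where the HA holds it, date of last HA contact, and dates of cardiovascular and renal complications. Define those complications and state that fatal cardiovascular and renal events count.

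Count attendances from the index date to the earliest of death, last contact or data cut, and compare rates per person-year, for example by negative binomial regression with log person-time as offset. Read any before-and-after change against the controls: everyone survived the baseline year, so counting use before death can raise later rates whatever the programme does. Analyse complications as time to first event, with other death as a competing event. Report all-cause mortality by group.

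The cost is a few more fields in an extraction already planned and a slightly more complex model.
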